#### Subgroup analyses

Pre-specified subgroup analyses will be limited to comorbid conditions that affect management of fluid status – specifically heart failure and diabetic status – and will be assessed through an interaction term in the model [33]. They will also explore, in a separate analysis, the effects of unit-level practice patterns (Table 2) as defined by our pre-study survey of 66 dialysis units, e.g. routine use of blood volume monitors, BI, dialysate sodium concentration, including stated approaches to fluid management (e.g. intention to reduce weight to avoid the use of antihypertensive drugs).

#### Economic evaluation

Economic analysis will be carried out to explore the relative cost-effectiveness of the intervention compared to standard management. The base-case analysis will adopt an NHS and personal social services perspective [34]. Additional analyses will be undertaken from a wider societal perspective, by considering private (patient-incurred) costs and productivity loss, using added questions from a modified Client Services Receipt Inventory developed for patients with chronic kidney disease. Costs and benefits accruing in the future will be discounted to reflect positive time preference.

A trial-based analysis will be carried out alongside the BISTRO study to determining the cost-effectiveness of the compared strategies on the basis of patient-level data obtained within the study period. Results will be presented in the form of incremental cost-effectiveness ratios, reflecting the extra cost for an additional unit of outcome. The main outcome will be the QALY, determined from participants’ responses to the EuroQol EQ-5D-5 L [21] and SF-12 [35] instruments at baseline and 3-monthly thereafter. To account for uncertainty, the inherent uncertainty due to sampling variation, the joint distribution of differences in cost and outcomes (QALYs) will be derived by carrying out a large number of non-parametric bootstrap simulations [36]. Results will be depicted on a cost-effectiveness plane and will be plotted as cost-effectiveness acceptability curves (CEACs) [37]. CEACs will show the probability of the BI-guided and standard fluid management options being cost-effective across a range of possible values of willingness to pay for an additional QALY. Additional work will involve building a decision analytic model to assess costs and effects likely to accrue beyond the study follow-up period**.**

### Monitoring

The Keele CTU data management team will perform data quality checks of CRF data. Data queries will be entered to a log that will be sent to the trial manager, who will work with each site to resolve data queries in a timely fashion and provide further training as required. This, along with safety reports, will inform a risk-based approach towards assessing a need for any onsite monitoring visits. Trial monitoring reports will be reviewed by the Trial Management Group, Data Management Committee (DMC) and Trial Steering Committee (TSC). These committees are constituted according to NIHR Health Technology and Assessment Board guidelines and are fully (DMC) or >75% independent (TMC). The DMC will receive un-blinded safety data at the group level and the TMC will receive reports from the DMC.

## Discussion

Adoption of new technologies to support clinical management requires scrutiny no less than the introduction of new pharmacological interventions. Bioimpedance is not new, although the technology has become more sophisticated, and the actual process of taking measurements is both safe and reproducible in trained hands [12]. Introduction of this technology to the clinical setting has been found to be acceptable to patients and many dialysis units around the world are now undertaking regular measurements as part of clinical practice. The evidence that BI gives clinicians new information about their patients’ body composition is strong and it is increasingly clear that the combination of reduced lean tissue mass and excess extracellular water (ECW) in proportion to intracellular water (ICW) – however this is expressed (phase angle, ECW/ICW, overhydration index) –, is associated with worse clinical outcomes.

The question remains how to use this additional information in day-to-day clinical management. Should clinicians attempt to normalize measured ECW to the patient’s normally hydrated weight or should they deliberately volume-deplete patients by the end of their dialysis treatment in an attempt to control blood pressure and undo the damage associated with long-standing hypertension? Without an independent measure of body composition, how do clinicians know which of these strategies they are employing? Given the potential to cause harm by excessively and serially volume-depleting patients, it would seem crucial that this practice is properly evaluated in a clinical trial. BISTRO is designed to fill this knowledge gap, focussing on the simplest of potential casualties of volume depletion, residual kidney function, a commodity that has been shown to be of consistent benefit to dialysis patients.

Trials assessing fluid management are challenging to undertake. One of the reasons for this is that assessing fluid status and implementing change are an example of complex decision making. The clinician, working with the patient, needs to take several things into account (e.g. symptoms, dietary intake, multiple comorbidities, dialysis tolerance, conflicting diagnostic information) and choose from several interventions (e.g. salt restriction, increased or reduced fluid removal, pharmacological interventions, and often more than one). One of the lessons learned from the UK-Shanghai BI trial in peritoneal dialysis patients [17], which attempted to collect decisions made at the time of fluid status assessment, was just this –these decisions are complex, multiple and bi-directional over time. To try and understand this better for BISTRO we have developed a template that will both help clinicians order their approach to fluid assessment and clarify why they chose to over-ride the BI-derived normally hydrated weight. The disadvantage of this approach may be that fluid management is ‘improved’ in the control group, so putting the intervention under greater pressure to demonstrate a benefit; the advantage is a better understanding of the intervention and even if the study is negative we will have, for the first time, a validated template to support fluid management.

Performance bias is also a risk in this type of study, which has inevitably to be an open-label design. We have endeavoured to minimize this risk by separating the BI measurements from the clinical assessments and blinding both clinicians and participants to the BI measures in the control group. This will be a major focus of the training sessions that will be undertaken at all the sites, which will also ensure consistency in how the intervention is implemented.

Finally, in designing the trial we carefully considered the pros and cons of a cluster (dialysis unit) versus a patient-level randomisation. Apart from practical reasons (for example patients often transfer from the main dialysis unit to a satellite centre after initiation of treatment, potentially forcing either drop in or out of the intervention) we became aware of significant variation between sites in their approach to fluid management. We undertook a survey of UK dialysis units to establish this, confirming that the number of sites required to get a balanced cluster randomization would have been impractical [11]. We have, however, used the information from this survey to undertake an annual survey of practice patterns during the conduct of the trial to allow us to correct for these in the primary and secondary analyses. Understanding the interactions between these practice patterns and clinical outcomes are an additional, potentially useful benefit of the study.

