**Methods/Design:**

516 pateints commencing haemodialysis, aged >18 with RKF of > 3 ml/min/1.73 m^2^ or a urine volume >500 ml per day or per the shorter inter-dialytic period will be consented and enrolled into a pragmatic, open-label, randomized controlled trial. The intervention is incorporation of bioimpedance spectroscopy (BI) determination of normally hydrated weight to set a post-dialysis target weight that limits volume depletion, compared to current standard practice. Clinicians and participants will be blinded to BI measures in the control group and a standardized record capturing management of fluid status will be used in all participants. Primary outcome is preservation of residual kidney function assessed as time to anuria (≤100 ml/day or ≤200 ml urine volume in the short inter-dialytic period). A sample size of 516 was based upon a cumulative incidence of 30% anuria in the control group and 20% in the treatment group and 11% competing risks (death, transplantation) over 10 months, with up to 2 years follow-up.

Secondary outcomes include rate of decline in small solute clearance, significant adverse events, hospitalization, loss of vascular access, cardiovascular events and interventions, dialysis efficacy and safety, dialysis-related symptoms and quality of life. Economic evaluation will be carried out to determine the cost-effectiveness of the intervention. Analyses will be adjusted for patient characteristics and dialysis unit practice patterns relevant to fluid management.

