#### Unit-level survey of practice patterns

A unit-level survey will be completed annually for the project duration by the Lead Consultant for each dialysis Unit (see Table 2 for items).

**Table 2 Tab2:** Unit level practice patterns, measured annually: first completion just before the first patient is enrolled

Dialysate sodium concentration
• Is there a standard sodium concentration in your unit? • What is the concentration of sodium used most frequently? • What proportion of patients have an individualised sodium concentration? • If individual sodium used o If low, what reason? If high, what reason? o Is your practice to match the plasma sodium?
Nutrition and sodium intake
• Does your HD unit have a dedicated dietitian? If so, how much time per patient do they have? • Do you have a policy on sodium restriction? If so what is the advised intake? • Do you have a policy on fluid restriction? If so what is the advised intake? • What information/training is given to nurses on the HD unit about fluid/salt restrictions? • Are patients given written advice about dietary intake and restrictions?
Diuretics
• Are the majority patients with residual kidney function routinely prescribed loop diuretics? • What is the typical dose (e.g. Furosemide, Bumetanide)? • Do you routinely use other diuretics (metolazone, thiazides, aldosterone inhibitors)?
Incremental dialysis
• Is it routine practice in your unit to commence HD incrementally? • If so, is this to preserve residual kidney function? • What proportion of patients on your unit do (a) 1 or (b) 2 sessions per week in the context of incremental start?
Measurement of residual Kidney Function
• Do you routinely measure residual kidney function on your unit? If so how frequently? • If so, do you use this to reduce the (a) frequency, (b) length of dialysis sessions?
Assessment and prescription
• Do you have a standardised protocol for assessing fluid status in new HD patients? • Protocol or not, in addition to clinical assessment do you routinely use (a) bioimpedance – of so state device, (b) Chest Xray,(c) Echocardiogram (d) central vein diameter, (e) blood volume monitoring? • Who assesses fluid status on your unit (a) consultants (b) HD dedicated staff grades (c) HD nurses (d) training grade doctors.
Fluid management strategies

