#### Primary outcome

Time to anuria will be analysed on an intention-to-treat basis (as the primary analysis) and on an as-treated basis (as the secondary analysis) using competing risks survival analysis [32], to estimate the relative risk (as expressed by the sub-hazard ratio) of the outcome (anuria) in patients where BI is used compared to control patients, accounting for the competing risks (death, transplantation). Patients undergoing modality change or recovery will be censored at the point of treatment switch. The analysis will control for known baseline covariates affecting residual function [26, 29], i.e. age, race, sex, comorbidities (separately or using a validated scoring system), antihypertensive drug use (ACE inhibitors/ARBs, calcium antagonists) and diuretic use.

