#### Secondary outcomes

Difference in rate of decline in renal clearance will be analysed using a random slopes linear mixed model, with adjustment for baseline characteristics, as for the primary outcome. We will analyse the effect of randomization on fluid status and body composition as determined by BI (to ascertain the effect of the intervention on the fluid assessment decision) and undertake corresponding appropriate analyses of the other secondary outcomes such as (i) *dialysis-related symptoms and treatment efficacy* (e.g. inter-dialytic fluid gain, falls, post-dialysis recovery time), (ii) *critical events* such as cardiovascular events and interventions, access-related interventions/failures and death, and (iii) *patient-reported measures* (e.g. EQ-5D-5 L, SF-12, PAM, POS-S renal, CSRI CKD). In analysing the effect of the intervention on patient activation measures we will look to see if this is associated with objective measures of fluid management, e.g. inter-dialytic fluid gain which, following adjustment for comorbidity, is a surrogate measure of patient survival.

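### The protocol gives conflicting primary models: the Discussion corrects for unit practice patterns, the Statistical methods do not, and the randomisation centre is absent from the stated model

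*Protocol article*

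**What the plan says.** Two places say that practice patterns enter the main analyses.

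- Abstract, Methods/Design: "Analyses will be adjusted for patient characteristics and dialysis unit practice patterns relevant to fluid management". It does not say which analyses.
- Discussion, last paragraph: the investigators "undertake an annual survey of practice patterns during the conduct of the trial", and the purpose given is "to allow us to correct for these in the primary and secondary analyses". This is the only statement that names the primary analysis.

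The Statistical methods section reads differently.

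- Primary outcome: "The analysis will control for known baseline covariates affecting residual function [26, 29], i.e. age, race, sex, comorbidities", with the list ending at "antihypertensive drug use (ACE inhibitors/ARBs, calcium antagonists) and diuretic use". No unit-level term appears, and neither does centre.
- Secondary outcomes: the slope model is fitted "with adjustment for baseline characteristics, as for the primary outcome".
- Subgroup analyses: "They will also explore, in a separate analysis, the effects of unit-level practice patterns". The patterns are there described as defined by the pre-study survey of 66 units.

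The title of Table 2 gives the timing of the trial's own survey: "Unit level practice patterns, measured annually: first completion just before the first patient is enrolled". Under Allocation, patients are randomised individually 1:1 in permuted blocks stratified by centre.

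**The concern.** A confirmatory trial needs one identifiable primary model. Here a reader who starts from the Discussion expects a competing-risks model with unit practice terms, and a reader who starts from the Primary outcome section expects one without them. The two models estimate different conditional quantities. A sub-hazard ratio is non-collapsible: adding a covariate that predicts anuria can change the estimate and its p-value even when that covariate is balanced between arms. With significance set at p ≤ 0.05, a result near the threshold could depend on which statement was followed, and the published document would not show which model had been pre-specified.

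Two related gaps add to this. The source of the practice variable is not consistent (pre-study survey, pre-enrolment wave or later annual waves). And the one design factor that the randomisation used, centre, is not in the listed model.

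**Working it through.** **1. The plan's own figures.** These are checked to see whether the choice of model touches them.

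Inputs from Sample size: 10-month anuria of 30% (control) and 20% (intervention), competing risks of 11%, 90% power, two-sided 5%, 12 months' accrual plus 12 months' follow-up, and 5% loss.

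- Cause-specific monthly hazard = p/(p + c) × [−ln(1 − p − c)]/10.
- Control: 0.30/0.41 × (−ln 0.59)/10 = 0.03861. Intervention: 0.20/0.31 × (−ln 0.69)/10 = 0.02394.
- Hazard ratio = 0.02394/0.03861 = 0.620.
- Schoenfeld events = 4(1.960 + 1.282)²/(ln 0.620)² = 184.02, rounded up to 185.
- Mean probability of an observed event under uniform accrual = 0.3777. Then 185/0.3777 = 489.7, and 489.7/0.95 = 515.5, rounded up to 516.

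Both published figures reproduce. The formula has no covariate term, so 185 and 516 stay the same under either model.

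**2. The statements side by side.**

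| Place | Practice patterns in the primary model? | Source of practice data |
|---|---|---|
| Abstract | Implied (analyses in general) | Not stated |
| Discussion | Yes, primary and secondary | Annual survey during the trial |
| Primary outcome | Not listed | – |
| Secondary outcomes (slope) | Not listed; same set as primary | – |
| Subgroup analyses | Separate analysis | Pre-study survey of 66 units |

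The Discussion and the Primary outcome section give different covariate sets for the same analysis.

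**3. Timing of the survey.** Only the first wave comes before enrolment. Recruitment is planned over 12 months, so a wave at about month 12 falls after essentially all planned patients have been randomised. The document does not say which wave would be used.

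**4. Does either choice bias the comparison?** Randomisation is by patient within centre. A unit's survey answer is shared by its intervention and control patients, so practice patterns should be roughly balanced between arms. Leaving them out does not confound the contrast.

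**5. How centre can enter.** With 30 centres (Recruitment) and 185 events, the average is 185/30 ≈ 6 events per centre. Fixed effects would need 30 − 1 = 29 indicators, which is sparse. Stratifying the model by centre, or using a shared or random centre effect, accounts for the design factor without estimating 29 separate coefficients.

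**The case against.** The best defence is that the passages can be read together. The list in the Primary outcome section may close only the category of patient-level covariates, with the unit terms of the Abstract and Discussion added to it. The separate analysis under Subgroup analyses may concern effect modification, which can coexist with main-effect adjustment. Its reference to the pre-study survey may say only where the items came from. The Statistical methods also promise a predetermined analysis plan and analysis blind to allocation, and a condensed article may leave the choice and coding of items to that plan.

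Part of this stands. The subgroup sentence alone proves no conflict, the Abstract does not name the primary analysis, and nothing shows that a choice would be made after seeing results by arm. What does not stand is that the matter is merely left open. The Discussion names the primary analysis and promises a correction that the section defining that analysis does not contain. A plan following either one departs from the other.

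Two stronger readings should be resisted.

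- A reader might infer that adjusting for later survey waves would remove part of the treatment effect, since the trial's training and assessment template could change unit practice. The documents do not support this: training and template apply to both arms, and each survey answer is common to both arms of a unit. Nor do they say that a later wave would be used.
- A reader might infer from the length of Table 2 that hundreds of candidate primary models are in play. The document describes no selection among the items, so that number has no basis in it.

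**Conclusion.** The inconsistency is real and should be corrected. It concerns which primary model was pre-specified, not the validity of the randomised comparison. Its consequence is that the primary sub-hazard ratio and p-value are not tied to a single covariate set. The size of any difference depends on how strongly unit practice predicts anuria, which the document does not give, so no figure is offered. No stated number is wrong.

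The conclusion rests on reading the Discussion's promise as a statement about the model and the Primary outcome list as the model's covariates. If the list is taken to cover patient-level covariates only, the model is still not fixed, because neither the practice items nor the survey wave is then given. The omission of centre is a separate, smaller point: the stated model does not reflect the stratified randomisation.

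**What to change.** State one primary model and use it consistently in the Abstract, Primary outcome, Subgroup analyses and Discussion:

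1. Treatment plus the baseline covariates already listed under Primary outcome, accounting for randomisation centre by stratification or a shared or random centre effect, not by about 29 fixed indicators.
2. Carry the same baseline covariates to the slope model, as Secondary outcomes already intends.
3. Remove from the Abstract and Discussion the claim that the primary and secondary analyses are corrected for practice patterns.
4. Keep practice patterns as exploratory treatment-by-practice interactions, using the pre-enrolment survey of the unit where the patient was randomised. Naming that unit matters because the Discussion says patients often move from main to satellite units.

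The cost is mainly wording, with a little more analysis work for the centre term and minor sparsity in small centres. No extra data are needed, and the planned 185 events and 516 patients stay as they are.

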## Abbreviations

BCM: Body composition monitor
BI: Bioimpedance
BISTRO: Bioimpedance spectroscopy to maintain renal output (Trial acronym)
CANUSA: Canada USA study
CEAC: Cost-effectiveness acceptability curves
CRF: Clinical report form
CSRI: Client service receipt inventory
CTU: Clinical trials unit
DEXA: Dual energy X-ray absorptiometry
DMC: Data monitoring committee
ECF: Extra-cellular water
EQ-5D-5 L: European quality of life (Qol) 5 dimension 5 level score
GFR: Glomerular filtration rate
HD: Haemodialysis
ICW: Intracellular water
IPOS: Integrated palliative care outcome scale
MoCA: Montreal cognative assessment tool
NECOSAD: Netherlands cooperative study of adequacy in dialysis
PAM: Patient activation measure
QALY: Quality-adjusted life years
RKF: Residual kidney function
SF12: Short form 12 (Health Survey)
TSC: Trial steering group
